## Background

Spontaneous intracerebral hemorrhage (ICH), non-iatrogenic ICH without trauma, is the second most common and the most devastating form of all strokes with the poorest prognosis [1, 2]. Approximately 15% of all cases of spontaneous ICH occur in the thalamus [3–5]. The thalamus is a deep brain structure and is an important center for the transmission of neural signals [3, 6]. Due to its anatomical location and the vital functions that it performs, the decision of conservative or surgical management for TH remains controversial [2, 7, 8]. Management is influenced mainly by the clinical experience of the treating surgeon and the volume of the hematoma [9]. Patients with minor TH, especially volumes less than 10 cc, usually obtain favorable outcomes when treated with conservative measures. However, patients with major TH, greater than 30 cc, have mortality rates of more than 80%, no matter what treatment is selected [10]. Moderate TH (10–30 mL) constitutes more than half of all cases of TH, and these patients have a mortality rate of more than 30% [11]. As moderate TH is the most common form of TH, its prognosis carries the greatest weight in calculating the prognosis of all forms of TH. In patients with moderate TH, conservative treatment alone versus surgical treatment is naturally a difficult decision to make. Because surgical treatment is invasive, adjacent structures may be damaged and neural pathways may be disrupted during surgical evacuation of a hematoma, thereby aggravating the degree of neurologic deficits or creating new ones. Meanwhile, conservative treatment alone does not offer the involved thalamic tissue the same type of relief that evacuation offers and is therefore felt to be a limited strategy in improving neurologic function. The limitations of both therapeutic strategies provide considerable room for better approaches or combinations of approaches.

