Acupuncture, one of the major branches of Traditional Chinese Medicine (TCM), has long been used to treat acute stroke, including hemorrhagic stroke, in China as well as in many other East Asian countries. Acupuncture’s utility in the treatment of non-hemorrhagic stroke, which is now documented by the WHO (World Health Organization, 2002), has been widely researched [18]. In recent years, a number of studies using modern technologies have shown that acupuncture may have neuroprotective effects following hemorrhagic stroke as well [19–22]. One preclinical systematic review of 19 animal studies showed that GV20 (Baihui) based acupuncture can improve neurologic outcome by regulating the inflammatory response to a hematoma, inhibiting neuronal apoptosis, reducing cerebral edema, maintaining ATP supply, promoting nerve regeneration, maintaining neuronal membrane integrity, and promoting hematoma resorption [23]. In another animal study, acupuncture at the DU20 acupoint was reported to have a neuroprotective effect on cerebral hemorrhage by inhibiting Notch-Hes signaling in rat basal ganglia [24]. It has also been reported that electro-acupuncture treatment at the Zusanli (ST36) acupoint may accelerate ICH-induced angiogenesis via the up-regulation of the HIF-1α protein and therefore may enhance recovery following hemorrhagic cerebral injury [25]. A separate study confirmed that treatment at the ST36 acupoint may aid recovery following central nervous system intracerebral hemorrhage in rats [26]. Although animal studies have led to progress in determining how acupuncture exerts its benefits in the treatment of acute hemorrhagic stroke, the determination of its clinical value remains incompletely assessed [27–30].

To our knowledge, no organized study has reported on the effects of acupuncture in patients with acute moderate TH. Specifically, no prior study has examined whether or not the use of acupuncture combined with conventional treatments improves the prognosis of moderate TH patients compared to conventional treatments alone.

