### Study design

This study will be a single-center, randomized, placebo-controlled, parallel group, and patient-assessor-blinded clinical trial. After completing informed consent, 488 eligible patients will be recruited and randomized to one of eight groups: 10–15 cc left sided TH study group (*N* = 61) and a corresponding control group (*N* = 61), 10–15 cc right sided TH study group (*N* = 61) and a corresponding control group, 15–30 cc left sided TH study group (*N* = 61) and a corresponding control group (*N* = 61), and 15–30 cc right sided TH study group (*N* = 61) and a corresponding control group. The patients in each of the study groups will receive 36 sessions of Chinese acupuncture in addition to standard treatments for TH, which include anticonvulsant therapy, antihypertensives, osmotic diuretics for the management of intracranial pressure, and invasive treatments as necessary. The patients in each of the control groups will receive standard treatments only. Patients’ neurologic status will be assessed at baseline and at the end of treatment as well as at 30 day and 90 day follow-up intervals. CT imaging will be performed on admission and at 90 days follow up. All patients will be required to complete written informed consent prior to enrollment. If patients are unable to complete written informed consent, it will be obtained from their relatives. A flow chart demonstrating an outline of the study is included in Fig. 1.

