Another potentially confounding factor is the involvement of adjacent brain tissue as a secondary result of the initial thalamic insult. Adjacent brain tissue can necrose either directly via extension of the thalamic bleed or indirectly via mass effect from the thalamic bleed and/or edema related to the thalamic bleed. Areas at specifically high risk include the genu of the internal capsule which lies lateral to the thalamus, the posterior limb of the internal capsule which lies posterolateral to the thalamus, the anterior limb of the internal capsule which lies anterolateral to the thalamus, and the peri-thalamic/peri-ventricular white matter which lies superior to the thalamus. Involvement of the genu of the internal capsule, the posterior limb of the internal capsule, and adjacent white matter could result in paralysis. Involvement of the posterior limb of the internal capsule could also result in sensory loss or impaired comprehension [36]. Finally, involvement of the anterior limb of the internal capsule could result in cognitive issues. Involvement of any of these areas could potentially impact how a patient recovers and/or sway the post-stroke assessment scores in one direction or another depending on how many of the affected patients ended up in the control group or the intervention group. To combat this, we utilized two mechanisms. First, we excluded patients from the study whose TH on admission CT demonstrated extension of the insult beyond the thalamus. However, admission CT often does not disclose the true area affected by the insult. CT performed 90 days later is much more sensitive in demonstrating the insult’s true encompassment. We therefore further subdivided the groups by size. While all subjects in the study have moderate thalamic hemorrhage, groups were further subdivided into subjects with 10–15 cc of TH and 15–30 cc of TH. Patients with 10–15 cc of TH are much less likely to experience insults to brain tissue external to the thalamus than patients with 15–30 cc of TH as a result of the smaller size of the initial bleed. We also plan to retrospectively analyze the results of CT scans performed 90 days following the insult to determine what percent of patients in each group experienced extension of their primary insult to tissue beyond the thalamus and how this may have affected the results in that group. After dividing patients by side of hemorrhage and size of hemorrhage four intervention groups were established, and along with the corresponding four control groups, this totaled eight distinct subject groups.

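### Extension on the day-90 CT is a post-treatment finding, so using it to explain each group's NIHSS result can mislead that secondary interpretation

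*Protocol article*

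**What the plan says.** All references are to the protocol article.

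- **Discussion, status of extension.** "Another potentially confounding factor is the involvement of adjacent brain tissue as a secondary result of the initial thalamic insult". The worry given is that scores could shift according to how many affected patients fall in each arm. One route to such involvement acts "indirectly via mass effect from the thalamic bleed and/or edema related to the thalamic bleed".
- **Discussion, safeguards.** Two are named: excluding patients whose admission CT already shows spread beyond the thalamus, and dividing the groups at 15 cc. Both use baseline information.
- **Discussion, added analysis.** "We also plan to retrospectively analyze the results of CT scans performed 90 days following the insult", to find the percentage with extension in each group and "how this may have affected the results in that group". No adjustment, stratification or subsetting method is named.
- **Study design.** "CT imaging will be performed on admission and at 90 days follow up".
- **Acupuncture.** Treatment starts within 72 hours of onset and lasts six weeks.
- **Background, mechanism.** A review of animal studies is cited for acupuncture "reducing cerebral edema, maintaining ATP supply, promoting nerve regeneration, maintaining neuronal membrane integrity, and promoting hematoma resorption".
- **Background, prognosis.** For moderate thalamic haemorrhage, "these patients have a mortality rate of more than 30" per cent; no time point is given.
- **Dropout criteria.** Patients who deteriorate may be removed. Acupuncture patients are also removed for missing more than three sessions, a rule with no counterpart in the control arm.

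**The concern.** A confounder of a randomised comparison has to precede treatment. Extension first seen on the day-90 CT is recorded after treatment has ended, and the document's own rationale gives a route from acupuncture to it: less oedema, hence less damage to adjacent tissue. It is therefore a possible effect of treatment. The article's reasoning about how many affected patients land in each arm fits a baseline imbalance, and it is carried over to this variable.

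Two things could go wrong if a group's NIHSS result is explained by its day-90 extension. If acupuncture limits extension, part of its benefit would be put down to that group having had less extension, and the treatment would look weaker than it is. And only patients alive and still in the study at day 90 can have the scan, so the explanation rests on a selected set whose selection may differ by arm.

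**Working it through.** **1. The plan's own figure.** Sample size calculation gives SD 4.2, difference 2.3, 80% power and α = 0.05 (two-tailed, from Statistical analysis).

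n per group = 2 × (1.960 + 0.842)² × 4.2² / 2.3² = 52.4, so 53. Allowing for 10% non-adherence and 3% loss: 53 / 0.87 = 60.9, or 53 / (0.90 × 0.97) = 60.7; both round up to 61. Then 61 × 8 = 488, as stated. Nothing in this point changes it.

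**2. Order of events.** Admission CT → randomisation → acupuncture from within 72 hours, for six weeks → day-90 CT. Visible spread at admission is an exclusion, so any extension found at day 90 was not observed before treatment. With only two scans, damage that was present but hidden at admission cannot be told apart from damage that developed later.

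**3. Who can have the scan.** The document gives no day-90 mortality for this trial, so a range is assumed around its background figure, combined with its 3% loss to follow-up. Available scans = N × (1 − mortality) × 0.97.

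| Assumed deaths by day 90 | Of 61 per group | Of 488 |
|---|---|---|
| 20% | 47 | 379 |
| 30% | 41 | 331 |
| 40% | 36 | 284 |

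Removals under the dropout criteria could lower these further.

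**4. What conditioning on extension can do.** This is an illustrative simulation with 2 million patients per scenario. Its inputs are assumptions, not figures from the document: about 42% extension and 34% deaths in controls, extension adding 3 NIHSS points, and a shared unmeasured severity factor that raises extension, death and NIHSS. A score is generated for every patient, including those who die. Entries are control minus acupuncture; positive favours acupuncture.

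| Assumed action of acupuncture | Overall | Within extension strata, everyone | Within extension strata, survivors | Overall minus survivors |
|---|---|---|---|---|
| Direct effect 2.3; no effect on extension or death | 2.30 | 2.30 | 2.30 | 0.00 |
| Direct 2.0; extension 42% to 32% | 2.29 | 1.84 | 1.87 | 0.42 |
| Direct 1.6; extension 42% to 24% | 2.15 | 1.31 | 1.36 | 0.79 |
| As above, and deaths 34% to 24% | 2.14 | 1.30 | 1.24 | 0.90 |
| Direct 0; extension 42% to 24% | 0.54 | −0.31 | −0.25 | 0.79 |
| As above, and deaths 34% to 24% | 0.54 | −0.31 | −0.37 | 0.91 |

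The third row shows where the shift comes from. The overall effect of 2.15 is a direct 1.6 plus about 0.55 through extension. Stratifying removes the 0.55 and takes off about 0.3 more (1.6 to 1.31), because severity is no longer balanced between arms once extension is held fixed. So the stratified figure does not recover the direct effect either. In these scenarios restriction to survivors moves the result by only about 0.03 to 0.06, in either direction.

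**The case against.** The strongest reply is that the article does not commit to the harmful analysis. It announces a percentage per group and a tentative look at what extension may have done; it names no model and no split. A reader might infer that the day-90 CT is the plan's control for confounding, or that the planned analysis must give a biased answer. The text supports neither. The two named safeguards are baseline measures and the CT review is an addition to them. Bias also requires both that the comparison is actually conditioned on extension and that acupuncture alters extension or survival; the first row of the simulation shows none when it does not.

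Three further points stand.

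- The article says admission CT often misses the true extent of injury and that the later scan shows it better, and the inclusion criteria require bleeding to have stopped before acupuncture starts. Some day-90 extension is therefore likely to be old damage. The mediator argument rests on the oedema and mass-effect routes, and its support in the Background is animal data.
- The percentage with extension in each group is a legitimate description, and the eight groups already separate arm, size and side.
- The background mortality has no time point, and the trial restricts age, lesion site and organ failure. The scan counts above are therefore not upper limits.

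What the reply does not remove is the stated purpose. The look at extension is introduced under the heading of confounding and is meant to explain each group's results. That old and new damage cannot be separated is a reason for caution with the variable, not a defence of using it that way. How deaths are coded in an exploratory analysis can be left to a SAP, so that omission is not the point here.

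**Conclusion.** The point holds in limited form. Day-90 extension is measured after randomisation and treatment, is possibly in part an effect of acupuncture, and is missing for patients who die or leave before day 90. Calling it a confounder and using it to explain or split the NIHSS comparison can bias that secondary interpretation if acupuncture affects extension or survival.

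The document does not allow the size to be worked out. The 0 to 0.9 point range, against a design difference of 2.3, depends wholly on the assumed inputs, and the sign change appears only where all benefit runs through extension. A reader might infer that the trial's main result is at risk. It is not: the primary outcome is NIHSS, the listed tests carry no CT covariate, and 488 reproduces. This is a cheap improvement to a secondary analysis.

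**What to change.** Replace the sentence on the day-90 CT review with a few sentences to this effect:

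1. Extension on the day-90 CT is a post-treatment outcome. It will be reported by randomised arm within each size and side group, with all randomised patients in the denominator: extension, no extension, died before day 90, and alive without a scan (with reason).
2. The NIHSS treatment comparison will not be adjusted for, or subset by, day-90 extension. Any remaining look at extension and outcome is exploratory and carries no causal claim.
3. Baseline risk of extension will be addressed with admission haematoma volume and side as covariates. Side is fixed within a size and side group, so there only volume within the band contributes; both apply in any analysis pooled over groups.

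The word confounding should then be kept for what is known at admission.

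Cost: a few sentences and no new data, since volume, side and both scans are already planned. The downside is that the explanatory split by day-90 extension is given up or kept only as exploratory.

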## Trial status

Recruitment commenced in January 2017, and it is anticipated that the trial will be completed by March 2021.

## Abbreviations

CT: Computer tomography
GOS: Glasgow outcome scale
ICH: Intracranial hemorrhage
ICP: Intracranial pressure
MRI: Magnetic resonance imaging
STRICTA: Standards for Reporting Interventions in Clinical Trials of Acupuncture
TCM: Traditional Chinese Medicine
TH: Thalamic hemorrhage
WHO: World Health Organization
